### Statistical methods

#### Primary outcome

The primary analysis population will be the ITT population (see definition below). The primary endpoint is complete success at 24 months. Complete success is attained if all of the following conditions are met:IOP < 18 mmHg at 24 monthsSuccessful probing > 120° in case of microcatheter-assisted trabeculotomyNo change in surgical techniqueNo topical antiglaucomatous medication in treated eyeNo systemic antiglaucomatous medicationNo revision surgery

Absolute numbers, proportions of complete success at 24 months under each intervention, and difference in proportions will be reported and displayed in cross tables. Proportions of complete success will be compared using McNemar’s test, stratified by center.

The primary estimand addresses the primary objective, i.e., to demonstrate that microcatheter-assisted trabeculotomy is superior to probe trabeculotomy regarding complete surgical success at 24 months. The population consists of all children aged ≤ 12 years with primary or secondary childhood glaucoma, requiring bilateral glaucoma surgery. The anticipated intercurrent events “topical or systemic medication,” “revision surgery,” “necessary change of surgical technique,” and, in MCAT, “less than 120° successful probing” have all been integrated into the definition of complete surgical success and are thus addressed by the *composite strategy* which considers any of these possible events also as failure.

We do not expect center effects; potential period effects will cancel out because intervention allocation is balanced across periods. However, we will check for such effects in a sensitivity analysis using a conditional logistic regression model with treatment, period, and center as covariates.

In the primary analysis, participants’ missing values of complete success at 24 months will be imputed using multiple imputation. Multiple imputation will make use of available components of the endpoint at 24 months, the corresponding variables at earlier visits, treatment, demographic variables, and possibly further variables.

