**Methods:**

In this prospective, multicenter, observer-blinded, randomized controlled trial, 76 children (152 eyes) with bilateral primary or secondary childhood glaucoma aged ≤ 12 years will be included. Each child acts as own control using a paired-eye design: One eye is allocated to MCAT (experimental intervention), achieving a 360° trabeculotomy, the other eye to the probe trabeculotomy (control intervention) which enables a trabeculotomy over 90 to 120°. Each child receives both procedures (paired-eye design). The worse eye is treated first; the surgical method is randomized. Patients and observers are masked to the procedures. The patients are followed up for 24 months. The primary endpoint is complete success (IOP < 18 mmHg at 24 months without medication and revision surgery; with MCAT: successful probing of > 120° is also required for success) at 24 months of follow-up. The primary analysis is performed in the intention-to-treat population using McNemar test stratified by center.

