## Methods

### Aim, design and study setting

The aim of this study is to compare microcatheter-assisted 360° trabeculotomy with conventional probe trabeculotomy in children aged ≤ 12 years with primary or secondary glaucoma.

The primary hypothesis of this study is that MCAT is superior to probe trabeculotomy with respect to complete success at 24 months after surgery. The key secondary hypothesis is that MCAT is superior to probe trabeculotomy with respect to incomplete success at 24 months after surgery. Further secondary hypotheses address the superiority of MCAT with respect to complete and incomplete success at earlier time points and the superiority of MCAT with respect to other clinical parameters.

Four academic centers are contributing to the study. The coordinating center is the Department of Ophthalmology, University Medical Center Mainz (Germany), which is an academic hospital. Further centers are the Department of Ophthalmology, University Clinic Cologne (Germany), the Department of Ophthalmology, University Hospital Magdeburg (Germany), and the Department of Ophthalmology, UZ Leuven (Belgium).

A paired-eye design is used: each patient receives both interventions (experimental intervention in one eye and control intervention in the other eye in randomized sequence) and acts as his or her own control thus minimizing the influence of external factors on the outcome and the case numbers. The worse affected eye (i.e., higher IOP, longer axial length, greater corneal diameters, and greater cup-to-disc ratio) will be treated first; the investigator assesses which eye is worse affected.

To prevent selection bias, intervention sequence (probe TO, MCAT) will be randomized. Block randomization will be applied using variable block length and stratification by center. Sealed numbered envelopes generated by the coordinating center are provided containing which surgical technique must be used on the first and second eye, respectively.

To prevent observation bias, an independent observer masked to the intervention and not involved in the surgery will conduct the follow-up visits. At the slit lamp, a morphological differentiation between MCAT and probe TO is not possible and postsurgical treatments are the same after both procedures, so making this easily possible. Furthermore, patients, their parents, and their treating pediatricians and ophthalmologists are also masked to the intervention.

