#### Key secondary outcome

The analysis population will be the ITT population. The key secondary endpoint is incomplete success at 24 months. Incomplete success is attained if all of the following conditions are met:IOP < 18 mmHg at 24 monthsSuccessful probing > 120° in case of microcatheter-assisted trabeculotomyNo change in surgical technique

Absolute numbers, proportions of incomplete success at 24 months under each intervention, and difference in proportions will be reported and displayed in cross tables. Proportions of incomplete success will be compared using McNemar’s test, stratified by center.

Here, the key secondary objective is addressed, i.e., to demonstrate that microcatheter-assisted trabeculotomy is superior to probe trabeculotomy regarding incomplete surgical success at 24 months. The corresponding estimand’s population comprises all children aged ≤ 12 years with primary or secondary childhood glaucoma, requiring bilateral glaucoma surgery. By dropping the requirements of “no topical antiglaucomatous medication in treated eye,” “no systemic antiglaucomatous medication,” and “no revision surgery,” these intercurrent events are addressed by the treatment policy strategy. “Necessary change of surgical technique” and, in MCAT, “less than 120° successful probing” still constitute surgical failure, i.e., are addressed using the composite strategy.

In the primary and key secondary analysis, participants’ missing values of incomplete success at 24 months will be imputed using multiple imputation. Multiple imputation will make use of available components of the endpoint at 24 months, the corresponding variables at earlier visits, treatment, demographic variables, and possibly further variables. Details will be specified in the statistical analysis plan.

We do not expect center effects; potential period effects will cancel out because intervention allocation is balanced across periods. However, we will check for such effects in a sensitivity analysis using a conditional logistic regression model with treatment, period, and center as covariates.

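### The conditional logistic sensitivity model cannot check for centre effects and, at the plan's own inputs, will often give no finite treatment odds ratio

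*Protocol article*

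**What the plan says.** Under Primary outcome, the confirmatory comparison is fixed: "Proportions of complete success will be compared using McNemar’s test, stratified by center". The article then gives its view on nuisance effects, "We do not expect center effects; potential period effects will cancel out because intervention allocation is balanced across periods", and announces a check on that view: "we will check for such effects in a sensitivity analysis using a conditional logistic regression model with treatment, period, and center as covariates". The Key secondary outcome section repeats the approach for incomplete success, again "using a conditional logistic regression model with treatment, period, and center as covariates".

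Two design features in Aim, design and study setting matter here. The design is paired within the child: "each patient receives both interventions (experimental intervention in one eye and control intervention in the other eye in randomized sequence". Order is tied to severity: "The worse affected eye (i.e., higher IOP, longer axial length, greater corneal diameters, and greater cup-to-disc ratio) will be treated first". What the model calls period is therefore worse eye versus better eye.

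**The concern.** The sensitivity model is the only stated check of the assumption that centre and period do not matter, and it serves both the primary and the key secondary endpoint. A conditional likelihood carries no information on anything that is constant within the conditioning set, and centre is constant within a child. One of the two effects it is meant to examine is therefore out of its reach.

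The other difficulty is sparseness. The model uses only discordant pairs, and the plan expects very few that favour the probe. Splitting those by treatment order may leave an empty cell and an infinite or undefined odds ratio. If this is discovered after unblinding, any replacement model is post hoc.

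**Working it through.** **Inputs.** From Sample size: success 47% and 62%, 20% discordant pairs, correlation 0.63, 72 evaluable children, 5% dropout, 76 randomised. From Interim analysis: maximum 83. From Aim, design and study setting: four centres, randomised sequence, worse eye first.

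**Reproducing the plan's figure.** Let b be the probability of MCAT-only success and c that of probe-only success.
- b − c = 0.15 and b + c = 0.20, so b = 0.175 and c = 0.025.
- Both eyes succeed with probability 0.47 − 0.025 = 0.445. The correlation is (0.445 − 0.47 × 0.62) / √(0.47 × 0.53 × 0.62 × 0.38) = 0.1536 / 0.2423 = 0.634.
- Exact two-sided McNemar power at 72 pairs is 80.6%, and 72 / 0.95 = 75.8, i.e. 76.

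The sample size is internally consistent and matches a plain McNemar test.

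**Step 1: centre in the conditional model.** Write the logit of success for an eye as child effect + τ·treatment + π·period + γ·centre. For a discordant pair, the conditional logit that the MCAT eye is the success depends only on within-pair differences: τ ± π + γ·(centre − centre) = τ ± π. With three dummies for four centres, the within-pair design has five columns and rank 2, and every centre column is zero. No data can make γ estimable. Conditioning on centre instead of child would not help, since centre is constant within that stratum too.

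**Step 2: does the rest of the model have a finite estimate?** With treatment and period the model is saturated. In one sequence the logit is τ + π and in the other τ − π, so the estimate of τ is ½[ln(b1/c1) + ln(b2/c2)], where b1, c1, b2, c2 are the discordant counts by sequence. All four must exceed zero. Expected totals at n = 72 are 72 × 0.175 = 12.6 and 72 × 0.025 = 1.8, so about 0.9 probe-only pairs per sequence.

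For a sequence group of m children, P(both directions occur) = 1 − (1 − b)^m − (1 − c)^m + (1 − b − c)^m.
- m = 36: 1 − 0.825^36 − 0.975^36 + 0.8^36 = 1 − 0.0010 − 0.4019 + 0.0003 = 0.597. P(no finite estimate) = 1 − 0.597² = 0.643.
- m = 38: 1 − 0.617² = 0.619.

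Holding the difference at 15 points, with balanced sequences and no eye-order effect:

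| Discordance | n = 72 | n = 76 | n = 83 |
|---|---|---|---|
| 18% | 82% | 81% | 78% |
| 20% | 64% | 62% | 58% |
| 22% | 48% | 45% | 40% |
| 25% | 29% | 27% | 22% |
| 30% | 12% | 10% | 8% |

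With treatment alone at 20% discordance and n = 72 the figure is 16%, so the split by order causes most of the problem. In a simulated random-intercept logit model calibrated to the planned rates, it rises to 70% with a first-versus-second-eye gap of about 8 points and 83% with about 15. With no treatment difference and no eye-order effect it is about 20%.

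**Step 3: centre stratification of McNemar's test.** The usual stratified statistic is [Σ(b_k − c_k)]² / Σ(b_k + c_k) over centres k, where b_k and c_k are counts. The sums are simply the overall counts. With 13 and 2 discordant pairs, close to the expected 12.6 and 1.8, it is 11² / 15 = 8.067 however the pairs fall across centres.

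**Step 4: eye order and the primary test.** Balance removes bias from order, but the order effect stays in McNemar's variance. The documents give no eye-order gap, so these are assumed gaps (20,000 simulated trials, 72 pairs, same random-intercept model, large-sample tests):

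| Gap (points) | McNemar size / power | Order-adjusted size / power |
|---|---|---|
| about 8 | 4.0% / 84.4% | 4.8% / 85.3% |
| about 15 | 3.5% / 78.8% | 4.9% / 82.0% |

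A latent-normal model (correlation 0.9, assumed) gives 87.1% versus 88.7% power at 8 points, and a loss of about 4 points at 16.

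**The case against.** The strongest reply on the sensitivity model is that the article names a model, not an estimation method, and that the method belongs to an analysis plan that is not shown and is due before database lock. That stands for the non-finite estimate: exact, likelihood-ratio or penalised inference on the same model still yields a p-value and a bound. It is also fair that the 64% holds only at 20% discordance with the full 15-point effect, and that the Interim analysis section itself admits little prior knowledge of discordance. Neither reply rescues the centre term, because no estimation method recovers a coefficient that is absent from the likelihood.

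Three stronger inferences are tempting, and the documents do not support them.
- A reader might infer that the primary test is invalid or should be replaced because eye order is left out. The statement that "potential period effects will cancel out because intervention allocation is balanced across periods" is right for bias, and McNemar keeps its type I error at or below nominal. Gaps large enough to cost much power also push discordance above the planned 20%: in the latent-normal model, 16 and 24 points give about 23% and 28%. Part of any fall in power is then higher discordance, not the omission of order.
- A reader might take the centre stratification to mean a sum of centre-wise statistics on 4 df, with a serious loss of power. The article never states that form, and its sample size matches the plain test.
- A reader might carry the 64% over to the key secondary endpoint. No discordance is given for incomplete success, so no figure can be derived. Only the centre argument carries over.

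**Conclusion.** The point holds for the sensitivity model. The announced check for centre effects is impossible for both endpoints. This follows from the pairing and needs only that the model conditions on the child, as the paired design implies.

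For the primary endpoint, ordinary maximum likelihood for treatment plus period is more likely than not to have no finite estimate at the planning values. That conclusion assumes balanced sequences, the full planned effect and no eye-order effect. It reverses at n = 72 once discordance reaches about 22%.

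The primary McNemar test stands. It may be mildly conservative because "The worse eye is treated first; the surgical method is randomized", at a cost of about 1–2 points of power for an 8-point eye-order gap and 3–4 points for a gap of about 15–16. Those gaps are assumptions. Severity is moderate to minor: a stated analysis cannot do what it is said to do, but the confirmatory conclusion does not depend on it.

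**What to change.** - In both outcome sections, delete the centre main effect from the conditional logistic model.
- Examine centre through treatment-by-centre differences, for example centre-specific paired differences with an exact or penalised interaction test. Ordinary maximum likelihood will not serve here either: with four equal centres (assumed), n = 72 and 20% discordance, a treatment-by-centre model lacks a finite estimate in at least 98% of trials.
- Fit the treatment-plus-period model by exact or Firth-penalised conditional logistic regression, named in advance.
- Keep the pooled McNemar test as primary. Either state that centre stratification means the pooled 1-df statistic, identical to plain McNemar, or delete the phrase.
- Optionally, prespecify an eye-order-adjusted paired test of Mainland-Gart or Prescott type as supportive, and limit the cancelling-out claim to bias.

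The cost is wording in the protocol and the analysis plan before database lock. Centre and sequence are already known from the stratified randomisation, so no new data are needed and the sample size is unchanged.

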#### Key secondary outcome

The analysis population will be the ITT population. The key secondary endpoint is incomplete success at 24 months. Incomplete success is attained if all of the following conditions are met:IOP < 18 mmHg at 24 monthsSuccessful probing > 120° in case of microcatheter-assisted trabeculotomyNo change in surgical technique

Absolute numbers, proportions of incomplete success at 24 months under each intervention, and difference in proportions will be reported and displayed in cross tables. Proportions of incomplete success will be compared using McNemar’s test, stratified by center.

Here, the key secondary objective is addressed, i.e., to demonstrate that microcatheter-assisted trabeculotomy is superior to probe trabeculotomy regarding incomplete surgical success at 24 months. The corresponding estimand’s population comprises all children aged ≤ 12 years with primary or secondary childhood glaucoma, requiring bilateral glaucoma surgery. By dropping the requirements of “no topical antiglaucomatous medication in treated eye,” “no systemic antiglaucomatous medication,” and “no revision surgery,” these intercurrent events are addressed by the treatment policy strategy. “Necessary change of surgical technique” and, in MCAT, “less than 120° successful probing” still constitute surgical failure, i.e., are addressed using the composite strategy.

In the primary and key secondary analysis, participants’ missing values of incomplete success at 24 months will be imputed using multiple imputation. Multiple imputation will make use of available components of the endpoint at 24 months, the corresponding variables at earlier visits, treatment, demographic variables, and possibly further variables. Details will be specified in the statistical analysis plan.

We do not expect center effects; potential period effects will cancel out because intervention allocation is balanced across periods. However, we will check for such effects in a sensitivity analysis using a conditional logistic regression model with treatment, period, and center as covariates.

The intention-to-treat (ITT) population will include all randomized children aged ≤ 12 years who meet the inclusion criteria and are assigned to either the MCAT or PT treatment arms, regardless of whether they complete the treatment as per protocol, receive the assigned intervention, are lost to follow-up, experience protocol violations, or (not) adhere to the follow-up schedule. Children who are randomized but subsequently found to be ineligible post-randomization (e.g., misdiagnosed or found not to have childhood glaucoma) will be included in the ITT analysis unless consent is withdrawn or data is unavailable.

#### Further secondary outcomes

See Supplemental Material 1.

All analyses of secondary endpoints will be interpreted exploratory. The statistical analysis plan will be finalized before database lock.

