### Sample size

El Sayed and Gawdat [8] observed 14 complete successes in 30 eyes at 2 years (47%) treated conventionally and 18 complete successes in 29 eyes treated with MCAT (62%—counting as failures those eyes in which less than 120° was possible). Therefore, we also aim to establish a difference in success rates of 15% at the 5% significance level with 80% power. In our previous experience, at most 20% of outcomes differ between both eyes of a patient. Therefore, we assume that the proportion of discordant pairs (i.e., success only with one technique in a patient) is 20%. This is equivalent to a correlation of 0.63 given overall probabilities of success of 47% and 62%.Power calculation has been performed using SAS PROC power. We found that with 72 patients and a correlation of 0.63 between eyes there is 80% power to detect an increase from 47% success rate to 62% success rates at the 5% level.We assume a dropout rate of 5% due to the empirically excellent adherence of the patients. Therefore, 76 patients are to be randomized in this study. The expected CONSORT flow diagram is presented in Fig. 2.

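### The key secondary objective is to demonstrate superiority, but the plan makes every secondary analysis exploratory, so read literally it cannot meet that objective

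*Protocol article*

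**What the plan says.** Three places in the protocol article bear on the status of incomplete success at 24 months.

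- **Aim, design and study setting** has three tiers: a primary hypothesis, one key secondary hypothesis, and further secondary hypotheses. The middle tier reads: "The key secondary hypothesis is that MCAT is superior to probe trabeculotomy with respect to incomplete success at 24 months after surgery".
- **Key secondary outcome** gives this endpoint the ITT population, multiple imputation, its own estimand with a strategy for each intercurrent event, and the same centre-stratified McNemar test as the primary. The objective is "to demonstrate that microcatheter-assisted trabeculotomy is superior to probe trabeculotomy regarding incomplete surgical success at 24 months". The primary objective uses the same verb, to demonstrate.
- **Further secondary outcomes** then states: "All analyses of secondary endpoints will be interpreted exploratory". No exception is made for the key secondary endpoint.

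The 5% level and the power appear only for complete success. Sample size says "we also aim to establish a difference in success rates of 15% at the 5% significance level with 80% power", and Interim analysis repeats this for the same 15-point difference.

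**The concern.** An analysis declared exploratory can suggest or support a finding, but it cannot demonstrate superiority in the sense in which the primary analysis does. The article gives the key secondary endpoint a confirmatory objective and an exploratory status.

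Incomplete success drops the conditions on glaucoma medication and revision surgery, so it answers a different question from the primary endpoint. The article expects the trial to help establish MCAT as a standard therapy and to inform guidelines. Readers of the results will therefore need to know whether a significant difference on this endpoint is a claim or a signal. If that stays open, it may be settled after the data are seen. If the literal rule is followed, the trial gives up a claim it set out to make and could have kept without charge to the primary test.

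**Working it through.** **1. The plan's own figure.** Inputs from Sample size: success 47% (probe) and 62% (MCAT), between-eye correlation 0.63, 5% level, 72 evaluable pairs, 5% dropout.

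- Both eyes succeed: p11 = 0.47 × 0.62 + 0.63 × √(0.47 × 0.53 × 0.62 × 0.38) = 0.2914 + 0.63 × 0.2423 = 0.444.
- Discordant cells: 0.47 − 0.444 = 0.026 (probe only) and 0.62 − 0.444 = 0.176 (MCAT only). The total is 20.2%, in line with the stated 20%.
- Power of the exact conditional McNemar test = Σ over m of P(m discordant pairs out of 72) × P(test rejects in favour of MCAT, given m). At two-sided 5% this is 80.0% for 72 pairs and 79.3% for 71.
- 72 / 0.95 = 75.8, rounded up to 76.

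The stated "80% power to detect an increase from 47% success rate to 62% success rates at the 5% level" with 72 patients is reproduced. The article does not state sidedness. Of the variants tried, only the two-sided exact test gives 72; for 20% discordance the asymptotic McNemar formula gives 68 two-sided and 53 one-sided.

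**2. Error rate as written.** On the literal reading there is one confirmatory test, complete success at 5%. Error for confirmatory claims is 5%.

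**3. Error rate under a fixed sequence.** Test complete success at two-sided 5%, and incomplete success at two-sided 5% only if the first test is significant.

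- If the primary null is true, any false claim requires a false rejection of the primary: at most 5%.
- If the primary null is false and the key secondary null is true, the only possible false claim is on the key secondary endpoint: at most 5%.

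So the family-wise error is at most 5%, provided each test holds its own level. A simulation with 72 pairs, the asymptotic McNemar test and assumed joint outcomes agrees. With both nulls true (20% discordance on each endpoint), the family-wise error was 4.6%. With the primary effect present and the key secondary null true, false key secondary claims occurred in 3.6%.

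The primary test comes first at its full level, so its 5% level, 72/76 patients and 80.0% power do not change.

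**4. Power for the second claim.** The article gives no success rates or discordance for incomplete success, so these are assumptions. For a difference d and discordance D, the discordant cells are (D + d)/2 and (D − d)/2. Exact two-sided McNemar power with 72 pairs, for the test on its own:

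| Difference | D = 15.1% | D = 20% | D = 25% |
|---|---|---|---|
| 15 points | 97% | 81% | 68% |
| 10 points | 50% | 39% | 32% |
| 5 points | 12% | 10% | 9% |

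In the sequence, the chance of the second claim cannot exceed these values, nor the power of the primary test.

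**The case against.** The case for leaving the text alone has four parts.

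- **Exploratory status is legitimate.** A sponsor may decline a second confirmatory claim, above all for an endpoint with no stated power. This stands, and it is why the point is minor.
- **Superiority wording does not by itself mark a confirmatory test.** The article also words its further secondary hypotheses as superiority, and an endpoint can have its own estimand and test and still be exploratory. This stands in part. What it does not explain is the verb shared with the primary objective and the separate tier.
- **The sentence may be meant narrowly.** It stands under Further secondary outcomes, after a separate section for the key secondary endpoint. That may be the intention, but the word *all* does not say so. On the narrow reading the contradiction disappears, and the testing order may be in the analysis plan, which is not shown. Its absence from the article is not held against the plan here.
- **Promotion to confirmatory status is not the only cure.** Correct: rewording the objective would also remove the conflict.

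A reader might go further and infer that the plan inflates the type I error, for instance to 1 − 0.95² = 9.75% for two independent 5% tests. The documents do not support this. Nowhere does the article propose two unordered confirmatory tests, and its literal rule allows only one. Independence is also a poor model, because every eye with complete success also meets the definition of incomplete success. Inflation would arise only if superiority on incomplete success were claimed as confirmatory despite the exploratory rule.

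**Conclusion.** The inconsistency holds on the literal reading: the article sets out to demonstrate superiority on incomplete success and then rules out a confirmatory reading of that result. It is minor. It is a mismatch of wording and a forgone claim, not an error in the primary analysis, and it raises no error rate.

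The gain from a fixed sequence is free with respect to primary level, sample size and primary power. That is not a promise of adequate power for the second claim: under the assumed 20% discordance, power falls from about 81% at a 15-point difference to about 39% at 10 points and 10% at 5 points. The conclusion assumes that the exploratory sentence means what it says and that the analysis plan has not already settled the matter.

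**What to change.** Before any unblinded treatment comparison, make two edits in the protocol and carry them into the analysis plan, which the article says will be finalized before database lock:

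1. In Key secondary outcome, state that incomplete success at 24 months is tested at the two-sided 5% level only if complete success is significant at the two-sided 5% level, and that the result is then confirmatory.
2. In Further secondary outcomes, restrict the exploratory sentence to the further secondary endpoints.

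The cost is two sentences. No patients are added and the primary test gives up nothing. If the primary test fails, the key secondary result is exploratory, which is no worse than the present rule. It would help to add that the trial was not sized for this second test.

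If the sponsor prefers to keep the endpoint exploratory, reword the key secondary objective so that it estimates or explores the difference instead of demonstrating superiority. Either choice removes the conflict.
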